
Based on these, we conducted a prospective cohort design, combined with perioperative multi-time point POCUS monitoring of diaphragm function, to explore the correlation between PDD and PPCs after minimally invasive thoracic surgery (VATS and RATS). Additionally, the risk factors for PPCs will be screened out, by integrating perioperative diaphragm ultrasound monitoring with ARISCAT, we also aim to verify whether this predictive efficacy will be improved.

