### Study design

2.1

This was a non-randomized, single-center, prospective observational study conducted at the Affiliated Cancer Hospital of Guangzhou Medical University. One hundred and forty-eight patients who underwent elective pulmonary resection for lung disease between July 2025 and May 2026 were included. Figure 1 is the study timeline. Bilateral diaphragm function was monitored by ultrasound at 4 time periods, 1st day before surgery (T0), 30 min post-extubation in the Post-anesthesia Care Unit (PACU) (T1), 1st day after surgery (T2), and 3rd day after surgery (T3). This standardized T1 measurement window will be uniformly applied to all enrolled patients in the study. Diaphragm thickness at the end of inhalation (DTei), diaphragm thickness at the end of exhalation (DTee), and DE during voluntary calming respiration were recorded at each time period. The occurrence of patients’ PPCs was tracked and observed during the 7 day postoperative period, and related clinical variables were recorded, respectively. Figure 2 is the trial flow chart.

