### Sample size calculation

2.8

Sample size is recalculated based on the primary predictive objective (logistic regression for the association between PDD and PPCs). Based on the literature review of perioperative PPCs incidence in minimally invasive thoracic surgery (VATS/RATS) with standardized EPCO complication definitions and complete 7-day postoperative follow-up and our pilot study, the baseline PPC incidence of 37% was selected as the core assumption for this power analysis and sample size calculation; Assuming a PDD incidence of 30% postoperatively (7, 12), a PPCs incidence of 37% in the study population (1–5, 15, 32), an odds ratio (OR) of 3.0 for PDD predicting PPCs (7, 28), alpha = 0.05, power = 0.80, and 10% dropout rate, a minimum of 148 patients in total is required. Sample size estimation is performed using PASS software (PASS 15 Power Analysis and Sample Size Software (2017). NCSS, LLC. Kaysville, Utah, United States)^1^ with logistic regression parameters accounting for covariates (age, BMI, ASA classification), and the above parameter selection fully aligns with the literature review results of PPCs incidence in minimally invasive thoracic surgery, ensuring the consistency between clinical evidence and statistical methodology.

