### Statistical analysis

2.9

Percentages will be calculated for dichotomous data and analyzed by the Pearson chi-square test or Fisher exact test. Continuous variables will be expressed as mean standard deviation (Mean ± SD) and median (ranging from 25th to 75th percentiles), and Student’s *t*-test was used for comparison between groups; The paired sample *t*-test is used for comparison of the same index. Propensity Score Matching (PSM) will be performed to balance baseline characteristics (e.g., age, BMI, ASA classification, tumor complexity) between the VATS and RATS groups (1:1 matching ratio, caliper width 0.2 SD) to mitigate selection bias. A baseline characteristics table will be added as Table 1 in the final manuscript, which will present the demographic, clinical and surgical-related baseline data of the VATS and RATS groups before and after PSM matching, so as to clearly show the balance effect of the matching process on the baseline characteristics between the two groups. Multivariate regression models will further adjust for residual confounding variables not fully balanced by PSM. Spearman and Pearson correlation analyses are used for the correlation analysis of normal distribution variables and non-normal distribution variables, respectively. Differences in diaphragmatic function parameters (DE, DTF) across multiple time points (T0–T3) will be analyzed using Linear Mixed-Effects Models (LMM) to account for within-subject correlation of repeated measures and robustly handle missing data. Differences in DEs at different times in the same subject were assessed by the Wilcoxon signed-rank test for matched data. Associations between postoperative DE reduction and clinically significant perioperative variables were analyzed using binary logistic regression analysis and reported as estimated crude advantage ratios and relative 95% CI. Similarly, binary logistic regression with stepwise variable selection (forward method) will be used to explore risk factors for PPCs, following the “Rule of Ten” (at least 10 events per candidate variable) to avoid model overfitting. To determine the predictive power of ultrasound parameters for PPCs, ROC curve analysis will be performed to validate the predefined PDD threshold (DE < 10 mm) rather than seeking a new cut-off, evaluating its discriminatory ability for PPCs. For the correlation analysis between diaphragmatic ultrasound parameters (DE, DTF) and ARISCAT scores, Pearson correlation analysis will be adopted if both variables conform to normal distribution, and Spearman correlation analysis will be used if the distribution is non-normal. On this basis, a combined predictive model for PPCs will be constructed by integrating ultrasound parameters (DE, DTF) and ARISCAT scores, and Net Reclassification Index (NRI) and Integrated Discrimination Improvement (IDI) will be used to quantify the improvement of the combined model in the discriminatory ability of PPCs prediction compared with the ARISCAT score single-factor model; the area under the ROC curve (AUC) of the single-factor model and the combined model will be further compared to verify the predictive efficacy of the integrated approach.

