We emphasize the importance of performing diaphragm ultrasound in perioperative patients with thoracic surgery, a high-risk group for PPCs, to demonstrate the clinical efficacy of POCUS during the perioperative period. This includes preoperative risk stratification and early postoperative PDD detection. Establishing standardized evaluation criteria is also crucial for guiding the targeted and effective application of POCUS in perioperative care. Our pre-experiments demonstrated that DE has higher feasibility and reproducibility in the postoperative environment when used for PDD exploration. It is reported that interobserver reliability has been shown to yield a bias below 0.1 cm with limits of agreement (LOA) of ±0.3 cm for DE, compared to a bias of −2% and wider LOA of ±21% for DTF (35). Therefore, DE serves as our primary measurement metric for assessing PDD. We acknowledge that DE only recorded during voluntary calming respiration without performing and recording “Deep Inspiration” or “Sniff Maneuver” at each time point is a significant limitation. Observed diaphragmatic dysfunction based on voluntary calming respiration may be exacerbated by postoperative pain and chest tube discomfort, which leads to difficulty in distinguishing between true diaphragmatic weakness and pain-induced restricted breathing (splinting) in the early postoperative period and thus limits the ability to isolate intrinsic diaphragmatic contractility. Additionally, although a peripheral adductor hallucis train-of-four ratio ≥0.9 is the clinical gold standard for safe extubation and sugammadex is administered to reverse neuromuscular blockade, the differential recovery between peripheral muscles and the diaphragm may lead to overestimation of surgical diaphragmatic dysfunction at the T1 (30 min post-extubation) time point; this potential pharmacological noise remains a theoretical possibility that needs to be considered when interpreting early postoperative POCUS results of diaphragmatic function. However, DE is heavily influenced by paradoxical movement and chest wall mechanics after thoracic surgery, which may reflect passive displacement rather than active diaphragmatic dysfunction. In contrast, DTF directly measures diaphragmatic muscle contractility—a key physiological parameter of active function. This limitation is addressed by analyzing DTF as a complementary metric to DE, ensuring comprehensive assessment of diaphragmatic function beyond passive excursion. Furthermore, we will investigate the potential of DTF as a diaphragmatic contraction force to provide additional insights for related research. The ARISCAT score is currently the most widely used tool for assessing the risk of postoperative complications (PPCs) in surgical patients, which showed good discrimination with AUC 0.83 (95% CI 0.79–0.86) on a receiver-operating characteristics curve and the accuracy was also good with a Brier score of 0.19 (34). To demonstrate the incremental predictive value of integrating POCUS parameters with the ARISCAT score, Net Reclassification Index (NRI) and Integrated Discrimination Improvement (IDI) will be used to quantify whether the addition of diaphragmatic ultrasound indicators (e.g., DE, DTF) significantly enhances the discriminatory ability of the ARISCAT score alone. Finally, we hope to further improve the accuracy and applicability of PPCs risk stratification by combining ARISCAT score with perioperative diaphragmatic function detected by POCUS.

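### NRI and IDI of nested models, with no optimism correction named, tend to show that ultrasound adds to ARISCAT even when it does not; the AUC comparison is only slightly affected

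*Protocol article*

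**What the plan says.** The Introduction gives the comparison with ARISCAT as a study aim: "we also aim to verify whether this predictive efficacy will be improved". Statistical analysis (2.9) sets out the method. First, "a combined predictive model for PPCs will be constructed by integrating ultrasound parameters (DE, DTF) and ARISCAT scores". This model is compared with one containing ARISCAT only: "Net Reclassification Index (NRI) and Integrated Discrimination Improvement (IDI) will be used to quantify the improvement of the combined model". The AUCs of the two models "will be further compared to verify the predictive efficacy of the integrated approach". The Discussion gives both indices a similar task: "quantify whether the addition of diaphragmatic ultrasound indicators (e.g., DE, DTF) significantly enhances the discriminatory ability of the ARISCAT score alone".

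The data come from one "non-randomized, single-center, prospective observational study" (Study design, 2.1), for which "a minimum of 148 patients in total is required" (2.8).

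Four things are not stated in the article:
- any split sample, cross-validation, bootstrap correction, shrinkage or second cohort;
- the type of NRI, or risk categories for it;
- the time point (T0 to T3) from which DE and DTF enter the model;
- which significance test, if any, goes with NRI and IDI.

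Two nearby safeguards do not cover this comparison. Validation is mentioned only for the DE cut-off of 10 mm. The rule of ten events per variable is attached to the stepwise risk-factor model, and it does not correct performance measured on the fitting data.

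**The concern.** The ARISCAT-only model is the combined model with the DE and DTF coefficients set to zero. Fitted by maximum likelihood to the same patients, the larger model can only follow those patients more closely, whether or not DE and DTF carry information. Indices computed on the fitting data count part of that extra fit as added discrimination. The usual z-tests for IDI and NRI make no allowance for it, so they can reject too often under the null.

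At stake is the claim that ultrasound improves on ARISCAT. The Conclusion links the study's findings to the use of diaphragmatic ultrasound in perioperative risk stratification, so an inflated gain would feed into that recommendation.

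**Working it through.** **Inputs from the article.** Total 148 patients, 10% dropout, "a PPCs incidence of 37% in the study population", PDD incidence 30%, OR 3.0, alpha 0.05, power 0.80 (all 2.8); ARISCAT AUC 0.83 (Discussion).

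**Assumptions.** Two-sided alpha; a second ARISCAT AUC of 0.70; DE and DTF at one time point (two added predictors); the usual z-tests.

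**Step 1: reproduce the sample size.** With overall PPC risk 0.37, PDD prevalence 0.30 and OR 3.0, the risks are p0 = 0.292 without PDD and p1 = 0.553 with it (0.7 × 0.292 + 0.3 × 0.553 = 0.37).

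n = (1.960 + 0.842)² × [1/(0.7·p0·(1−p0)) + 1/(0.3·p1·(1−p1))] / (ln 3)² = 132.6, so 133. Then 133/0.9 = 147.8, so 148.

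The plan's figure is reproduced and is not in dispute. Events: 0.37 × 148 ≈ 55, and 0.37 × 133 ≈ 49.

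**Step 2: indices.** Let p_A be the fitted risk from ARISCAT alone, p_C that from the combined model, and d = p_C − p_A.
- IDI = mean(d | PPC) − mean(d | no PPC). Its z is IDI divided by the root of the sum of the two squared standard errors.
- Continuous NRI = 2·[P(d > 0 | PPC) − P(d > 0 | no PPC)].
- AUC difference, tested by DeLong.
- Likelihood-ratio test of DE and DTF jointly, 2 df.

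**Step 3: null simulation.** 2,000 studies per setting, PPC 37%. ARISCAT is a normal score whose mean shift √2·Φ⁻¹(AUC) gives the chosen AUC; DE and DTF are independent noise. Both models are fitted and scored in the same patients.

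| | n=148, AUC 0.83 | n=148, AUC 0.70 | n=133, AUC 0.83 | n=133, AUC 0.70 |
|---|---|---|---|---|
| Mean IDI | +0.011 | +0.013 | +0.013 | +0.014 |
| IDI > 0 | 98% | 99% | 98% | 99% |
| IDI z > 1.96 | 10% | 12% | 10% | 13% |
| Mean continuous NRI | +0.22 | +0.19 | +0.23 | +0.20 |
| Continuous NRI z > 1.96 | 23% | 16% | 25% | 17% |
| Mean AUC difference | +0.006 | +0.011 | +0.006 | +0.012 |
| AUC difference > 0 | 87% | 88% | 84% | 84% |
| DeLong z > 1.96 | 0.3% | 0.4% | 0.2% | 0.5% |
| Likelihood-ratio p < 0.05 | 5% | 6% | 6% | 5% |

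The nominal rate for z > 1.96 is 2.5%; for the likelihood-ratio test it is 5%. In new patients scored with the n = 148 models, the AUC difference is −0.006 and −0.011 and IDI is about zero, so the apparent gains come from fitting.

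**Step 4: NRI type.** A two-category NRI cut at 37% (an assumed cut) exceeds z = 1.96 in about 3–4% of null studies, close to nominal.

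**Step 5: several time points.** With six noise predictors (DE and DTF at three time points, n = 148, AUC 0.83 / 0.70), z exceeds 1.96 for IDI in 56% / 66% and for continuous NRI in 69% / 56%. DeLong rises to 4% / 6%. The likelihood-ratio test stays at 6% / 5%.

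**Step 6: bootstrap optimism correction** (n = 148, AUC 0.83, two noise predictors, 400 studies, 100 resamples each).

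| | Apparent | Corrected |
|---|---|---|
| AUC difference | +0.006 (> 0 in 87%) | −0.006 (17%) |
| IDI | +0.012 (99%) | +0.0003 (38%) |
| Continuous NRI | +0.23 (94%) | +0.13 (75%) |

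The correction removes the false gain in AUC and IDI but only about half of it in continuous NRI, which is still +0.07 in new patients.

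**The case against.** The best defence is that the article nowhere says that performance will be left uncorrected. It names two models and three measures, and optimism correction is a detail that a full protocol or analysis plan could supply. That stands as a limit: the document does not rule out correction, and the figures above apply only if the indices are computed on the fitting data. The point survives because the text itself names IDI and NRI as the way to show a significant gain, in one cohort with no other data source. Choosing a continuous NRI would not be rescued by adding a bootstrap.

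A reader might also infer that the AUC comparison, to which 2.9 attaches the word verify, will falsely confirm the gain. The check does not support that for two added predictors: the bias is about 0.006 to 0.012, and DeLong rejects in favour of the larger model in under 1% of null studies. Nor is a false improvement certain; it is a strong tendency.

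Three further objections are fair. The NRI type is not given, and a two-category version behaves nearly correctly. A significance test for NRI and IDI is implied only by the Discussion, since 2.9 specifies none. And the ARISCAT comparison is neither the primary endpoint nor a listed secondary endpoint and does not drive the sample size; with one time point, three predictors and 49 events give about 16 events per predictor. These limit the consequence but do not remove the bias in IDI.

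**Conclusion.** The concern holds in a limited form. Computed on the fitting data, IDI is positive in about 98–99% of studies where DE and DTF add nothing. Its z-test favours the larger model at about four to five times the nominal rate (10–13% against 2.5%). A continuous NRI would average about +0.19 to +0.23 and be falsely significant in about 16–25%. False verification is therefore a problem of IDI and of continuous NRI, not of the AUC test. The absolute bias in AUC and IDI is small with two predictors and grows if several time points enter.

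This rests on fitting-data evaluation, standard z-tests, two added predictors from one time point, and an ARISCAT AUC of 0.83 or 0.70. The change should be made, but it does not threaten the primary endpoint.

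**What to change.** In 2.9, and in the matching sentence of the Discussion:

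1. Prespecify the time point at which DE and DTF enter, and test added value by the 2-df likelihood-ratio test of both added to ARISCAT.
2. Report the AUC difference and IDI corrected for optimism by a bootstrap that repeats the whole modelling process, including imputation, with confidence intervals.
3. Drop p-values for NRI and IDI, and drop continuous NRI, because bootstrap correction does not remove its bias. If a categorical NRI is kept, state its risk categories in advance and use it descriptively.
4. Replace verify with estimate wherever it describes the added value over ARISCAT.

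No new data or patients are needed. The cost is some extra R code, in software the plan already uses, and a smaller reported improvement.

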### Data collection and processing

2.10

We also recorded other parameters: age, gender, BMI, ASA classification, NYHA classification, metabolic equivalents (MET), preoperative comorbidities (COPD, chronic heart disease, chronic liver disease, metabolic disorders), pulmonary function, smoking history, Hb, SpO2, albumin, presence of respiratory infections in the previous month, ARISCAT score (33, 34), Arozullah score, surgical approach (VATS/RATS), surgical site and side, duration of surgery, extent of surgery, duration of intraoperative one-lung ventilation, amount of intraoperative rehydration and bleeding, extent of lymph node dissection, duration of postoperative chest tube drainage (to explore its potential association with diaphragmatic function), DE values during voluntary calming respiration at each time point (T0–T3), acoustic window adjustment records (if any) and left/right hemidiaphragm measurability status, duration of postoperative hospitalization and adverse events during the perioperative process. All data will be recorded in the same Excel sheet. Ultrasound images and videos will be copied from the ultrasound machine and stored on a removable hard disk for viewing.

## Conclusion

3

This study will elucidate the relationship between POCUS-detected PDD and PPCs in patients undergoing VATS and RATS. The findings may support the integration of diaphragmatic ultrasound into perioperative risk stratification and guide targeted preventive strategies to improve postoperative outcomes.

## Discussion

4

The higher incidence of PPCs in thoracic surgery patients is significantly associated with PDD (7, 9, 11, 35). We will use POCUS to specifically investigate the correlation between these two factors in minimally invasive surgery patients. As surgical techniques have evolved, the opportunities for clinical applications of RATS in thoracic surgery are increasing. In fact, according to a review of the Society for Thoracic Surgery General Thoracic Surgery Database 2023 (STS-GTSD), more than 80% of lobectomies, segmental resections, and wedge resections are performed through minimally invasive approaches (5). The feasibility of RATS lobectomy has been confirmed by several relevant studies in the last 5 years; compared to open thoracotomy, RATS seems to offer the same advantages as the VATS access (16). We will further evaluate the effects of these two surgical approaches on diaphragm function in surgical patients.

We emphasize the importance of performing diaphragm ultrasound in perioperative patients with thoracic surgery, a high-risk group for PPCs, to demonstrate the clinical efficacy of POCUS during the perioperative period. This includes preoperative risk stratification and early postoperative PDD detection. Establishing standardized evaluation criteria is also crucial for guiding the targeted and effective application of POCUS in perioperative care. Our pre-experiments demonstrated that DE has higher feasibility and reproducibility in the postoperative environment when used for PDD exploration. It is reported that interobserver reliability has been shown to yield a bias below 0.1 cm with limits of agreement (LOA) of ±0.3 cm for DE, compared to a bias of −2% and wider LOA of ±21% for DTF (35). Therefore, DE serves as our primary measurement metric for assessing PDD. We acknowledge that DE only recorded during voluntary calming respiration without performing and recording “Deep Inspiration” or “Sniff Maneuver” at each time point is a significant limitation. Observed diaphragmatic dysfunction based on voluntary calming respiration may be exacerbated by postoperative pain and chest tube discomfort, which leads to difficulty in distinguishing between true diaphragmatic weakness and pain-induced restricted breathing (splinting) in the early postoperative period and thus limits the ability to isolate intrinsic diaphragmatic contractility. Additionally, although a peripheral adductor hallucis train-of-four ratio ≥0.9 is the clinical gold standard for safe extubation and sugammadex is administered to reverse neuromuscular blockade, the differential recovery between peripheral muscles and the diaphragm may lead to overestimation of surgical diaphragmatic dysfunction at the T1 (30 min post-extubation) time point; this potential pharmacological noise remains a theoretical possibility that needs to be considered when interpreting early postoperative POCUS results of diaphragmatic function. However, DE is heavily influenced by paradoxical movement and chest wall mechanics after thoracic surgery, which may reflect passive displacement rather than active diaphragmatic dysfunction. In contrast, DTF directly measures diaphragmatic muscle contractility—a key physiological parameter of active function. This limitation is addressed by analyzing DTF as a complementary metric to DE, ensuring comprehensive assessment of diaphragmatic function beyond passive excursion. Furthermore, we will investigate the potential of DTF as a diaphragmatic contraction force to provide additional insights for related research. The ARISCAT score is currently the most widely used tool for assessing the risk of postoperative complications (PPCs) in surgical patients, which showed good discrimination with AUC 0.83 (95% CI 0.79–0.86) on a receiver-operating characteristics curve and the accuracy was also good with a Brier score of 0.19 (34). To demonstrate the incremental predictive value of integrating POCUS parameters with the ARISCAT score, Net Reclassification Index (NRI) and Integrated Discrimination Improvement (IDI) will be used to quantify whether the addition of diaphragmatic ultrasound indicators (e.g., DE, DTF) significantly enhances the discriminatory ability of the ARISCAT score alone. Finally, we hope to further improve the accuracy and applicability of PPCs risk stratification by combining ARISCAT score with perioperative diaphragmatic function detected by POCUS.

However, there are some limitations. For example, this is a single-center study that exclusively involves thoracic surgery; therefore, the generalisability may not be extrapolated. This is a non-randomized clinical study and selection bias may be present, which is mitigated by the inclusion of Propensity Score Matching (PSM) and multivariate covariate adjustment in the statistical analysis plan to balance baseline characteristics between the VATS and RATS groups. Additionally, we decided on a 7-day postoperative follow-up because most patients are discharged around 7 days after surgery. We acknowledge that limiting follow-up to the first 7 postoperative days may underestimate the duration or delayed impact of diaphragmatic dysfunction since postoperative diaphragmatic dysfunction has been reported in the literature to persist beyond the early postoperative period. We stopped POCUS monitoring at T3 (postoperative day 3) based on existing evidence (12, 24, 35) indicating that PDD reaches its peak within the first 72 h post-operatively and is most prominent within the first 3 postoperative days, with the dysfunction index tending to stabilize thereafter; moreover, early PDD (within 3 days) has been identified as a key predictor of subsequent PPCs including those developing at postoperative day 7 (7, 12), even those developing after day 3.
